### Qualitative methodology

Qualitative methodology study process using semi-structured interviews (figure 2):

1:1 interview with patients, clinicians, managers and other stakeholders involved in the remote ENT pathway.Interviews conducted on Microsoft Teams with audio recording for transcription.Analysis.

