**Methods and analysis:**

This single-centre, mixed-methods, prospective cohort study will be conducted at University Hospitals Birmingham NHS Foundation Trust. Remote clinics will use trained staff to collect diagnostic data (including endoscopic imaging and boothless hearing tests) for consultant review via secure cloud-based software. Quantitative analysis will assess patient outcomes, costs, waiting times, carbon footprint and satisfaction. Qualitative data from semi-structured interviews with patients, clinicians and managers will explore acceptability, scalability and barriers to implementation. The qualitative data will be analysed using the framework methodology, according to the non-adoption, abandonment, scale-up, spread and sustainability framework, while the strengthening the reporting of observational studies in epidemiology framework will be used to guide the reporting of quantitative data. Cost-effectiveness analyses will follow NICE guidelines, while environmental impact will be measurement will be informed by the sustainability in quality improvement framework. Recruitment will be aiming for 300 completed datasets and 30–35 interviews.

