### Secondary outcomes

Clinical throughput impact:Investigate impact of remote pathway on waiting times from referral to treatment.Compare the clinician time required per remote consultation to reach diagnosis/definitive treatment.Stakeholder acceptability:Examine barriers to implementation, training needs, scalability and throughput.Determine the optimal setting for data capture and assess geographic variation.Assess the impact across different demographics, especially under-served populations.Health economic analysis:Conduct a cost-consequences analysis detailing waiting times, quality of life, resource use, costs, time off work and productivity for both study groups.Perform cost-consequence and cost-utility analyses from an NHS perspective.Environmental sustainability:Calculate the direct (patient journey) and indirect (clinic output) carbon footprint of the ENT outpatient service by assessing carbon dioxide equivalents (CO_2_Eq) for both new and existing clinic models by location.

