This is an observational study, and we are not measuring the effect of an intervention. Our initial sample size calculations have been driven by similar pieces of implementation studies in the literature, looking into studies assessing non-inferiority interventions for remote/telehealth clinics, as well as assessing the potential financial benefit to the patients/service and the environmental impact,^11^,^15^ further informed by similar studies mapped through our team’s scoping review.^6^ Continuous sampling will be undertaken on both pathways until we reach a number of 150 participants from each group that have completed the initial questionnaires. The patients of the remote pathway will also be sent a follow-up questionnaire after their discharge, asking for their overall experience of the new service. The total of recruited participants will be expected to exceed the minimum of 300 we need for our analysis, and we will be allowing for a 10% attrition, as the current number for patients seen in face-to-face and remote clinics exceeds the 80 patients per cohort, per week. All the primary outcomes data will be extracted directly from the clinical notes of the patients, while the data of the secondary outcomes will be procured via questionnaires.

For the interviews, we will use a topic guide developed based on the existing literature and the research team’s experience of technology and innovation implementation, as well as service redesign.^16^,^18^ Through the interview process, we will investigate the experience of the different stakeholders involved in the remote pathway. We will undertake purposive sampling to select participants, expecting 30–35 participants in total, to allow for thematic saturation to take place.^19 20^ Participants in the interviews will be classified into two categories: patient participants and NHS staff. Recruitment will continue until overall thematic saturation has been achieved within each group. Patients enrolled will be approached, after completing the remote clinic pathway, while clinicians, managers and the other stakeholders will be given participation leaflets and invited via email or in person to participate in the study through interviews. If non-English speakers participate in the interviews, interpreters will also be facilitating the process.

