### Quantitative analysis

Quantitative analysis will examine patient characteristics, symptom resolution, discharge rates, consultant review volumes and waiting times, as well as environmental sustainability (assessed by the carbon footprint of clinics and patient travel).

Acceptability will be gauged using a 5-point Likert scale and open-ended questionnaires. Descriptive statistics (means, SD and CIs) will summarise continuous data, while discrete variables will be reported as counts and percentages. Standard regression models (95% CIs) and subgroup analyses will compare groups, with outcomes reported in scoring scales analysed as continuous variables. Count models will be used to count outcomes (such as number of appointments) and time-to-event models to assess time to definitive treatment/decision. A 5-point Likert scale questionnaire will further capture how different clinic permutations align with patient expectations. Missing data will be handled initially by descriptive means, aiming to describe the proportion of missing data, its characteristics and potential mechanisms and then using multiple imputation methodology. Analyses will adjust for age, sex, IMD quintile, baseline symptoms, presenting condition category, comorbidity count and distance to clinic; robustness will be checked using propensity score weighting. Differential follow-up will be handled with time-to-event methodology, using Cox proportional hazards, accounting for the differences in the follow-up duration across groups with different pathology.

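### Microsoft Teams is the only interview mode stated for patients, so those with poor digital access are likely to be under-represented in the interviews on acceptability and barriers

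*Protocol article*

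**What the plan says.** The Qualitative methodology section lists the interviewees as "1:1 interview with patients, clinicians, managers and other stakeholders involved in the remote ENT pathway" and then gives the mode: "Interviews conducted on Microsoft Teams with audio recording for transcription". The Qualitative analysis section relies on the platform's automatic transcription, with manual transcription as a fallback.

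On selection, the Recruitment section states: "We will undertake purposive sampling to select participants, expecting 30–35 participants in total, to allow for thematic saturation to take place". Patients come from those enrolled in the remote arm: "Patients enrolled will be approached, after completing the remote clinic pathway". Interviewing stops at thematic saturation, judged separately for patients and for NHS staff. The one access provision for interviews concerns language: "If non-English speakers participate in the interviews, interpreters will also be facilitating the process".

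On purpose, the abstract says: "Qualitative data from semi-structured interviews with patients, clinicians and managers will explore acceptability, scalability and barriers to implementation". Under stakeholder acceptability, the Secondary outcomes section includes: "Assess the impact across different demographics, especially under-served populations". The Quantitative analysis section names a second source on acceptability: "Acceptability will be gauged using a 5-point Likert scale and open-ended questionnaires".

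**The concern.** A single online mode selects interviewees on having a device, a connection and enough confidence to join a call. These traits bear on what the interviews are for. The study evaluates a digitally enabled service, asks in its Introduction whether some patient groups are better suited to it than others, and commits to examining under-served groups.

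If such patients decline or are never reached because of the mode, saturation among patients could be declared without their accounts. The barriers placed in the implementation framework would then come from a narrower group than the objective intends. No later analysis can repair this, because the missing accounts would not exist.

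**Working it through.** The article contains no figure to reproduce. The 30–35 interviews rest on saturation, not on a formula. The check therefore sets the relevant sections side by side.

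1. **Is Teams the only mode?** Yes, as stated. Qualitative methodology names Teams for all interviewees. Recruitment, Qualitative analysis and the abstract add no other mode. Recruitment provides interpreters, and Qualitative analysis provides translation and manual transcription. None of these deals with a patient who cannot join an online call.

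2. **Does the sampling plan counteract the mode?** Not on the text. Sampling is purposive, but no criterion for digital access or confidence is given. Even with such a criterion, a selected patient would still need another way to be interviewed, or help to use Teams.

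3. **Does the stopping rule counteract it?** No. Saturation is judged within patients as one group, so it can be reached among those who were able to take part.

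4. **Do the questionnaires fill the gap?** In part.
   - All recruited patients are asked to complete one on the clinic day, with 150 completers per group, so it does not depend on Teams. It includes ratings and open-ended items.
   - The interviews come after the pathway is complete and go deeper. They also supply the material for the implementation framework.
   - Remote-arm patients receive a second questionnaire after treatment or discharge, asking about the whole experience. The article says it is sent but not in what form, so its reach among these patients cannot be judged.

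5. **Can the effect be sized?** No. Two inputs are missing: the proportion of patients who could not manage a Teams call, and the number of patients among the 30–35 interviewees. For scale only, assume 15 patient interviews and a proportion of 10% to 25%. A sample in proportion would then hold 0.10 × 15 = 1.5 to 0.25 × 15 = 3.75 such patients. Both inputs are assumptions. The result is how many one would expect to hear from, not how many the plan would lose.

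**The case against.** The strongest case against the point has four parts.

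- **The pathway asks little digital skill of the patient.** The Introduction describes clinics that patients attend in person, where trained staff supervise the tablet history and the hearing test and record the ear and nose video. The cloud software is for the consultants. A reader might infer that those who cannot use Teams are the ones who struggle with the service, so that the interviews would flatter the remote pathway. The documents do not support that step: the two groups may overlap, but they are not the same. This part stands, and it removes any claim about the direction of bias.
- **Acceptability has a second source.** The questionnaires reach patients whether or not they can use Teams, and the planned subgroup analyses and adjustment for age and deprivation quintile also bear on the under-served objective. This stands as a partial offset, for the reasons given in the check.
- **No one is expressly excluded.** A reader might infer that digitally excluded patients cannot take part, or that none would be interviewed. The text does not say so. Digital access is not an eligibility criterion, and helped participation is not ruled out. Under-representation is the most that can be claimed.
- **A condensed article may leave alternative modes and sampling criteria to the full protocol.** This has some force for the sampling criteria, so their absence alone is not the point. It has less force for the mode, which the article does state, and states alike for patients and staff.

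**Conclusion.** The point holds in a limited form. Teams is the only interview mode stated for patients. Followed as written, this is likely to under-represent patients with poor digital access or confidence in the strand that explores acceptability and barriers, which sits badly with the objective on under-served populations. The questionnaires reduce the problem but do not remove it.

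The conclusion rests on two assumptions: that the stated mode is the one used, and that some eligible patients would find a Teams call hard to manage. Neither the size nor the direction of any bias follows from the documents. The effect is confined to the interview strand; the primary outcome data come from clinical notes and are not touched. The change is worth making because it is cheap before interviewing starts and the loss cannot be recovered afterwards.

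**What to change.** - In Qualitative methodology, state that interviews are held by Microsoft Teams, by telephone or in person, as the participant prefers, and that all are audio-recorded. Offering in-person interviews as well as telephone matters here, because some eligible patients have hearing problems.
- In Recruitment, add digital access or confidence to the purposive sampling criteria for patients.
- Report how many patients declined an interview, by reason, so that readers can see whether the mode played a part.

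The cost is a minor amendment, a recorder, and manual transcription of interviews held off the platform, which Qualitative analysis already permits where necessary. The drawback is that interviews in different modes may differ slightly in depth; recording the mode of each interview would let the analysts take this into account.

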### Qualitative analysis

MS Teams software provides auto-transcription of the interviews and NVivo software will be used to facilitate the data management. Professional translation will be available for non-English speakers and manual transcription will be undertaken if necessary. The data will be analysed using a directed content analysis to populate the NASSS framework using open matrix approach, as described by Elo *et al* and Assarroudi *et al*^21 22^ that will allow for the inclusion of emerging constructs within existing domains, including any project specific risks/challenges and opportunities identified by interviewees in the different groups. Any novel emergent themes will be recorded and coded into separate categories, allowing the classification of relevant information in the respective groups. We will compare themes within each group and between groups.

Two researchers (DS and IL) will independently allocate data within the framework. Any differences in coding will be discussed between the authors (DS, IL and SG) and a consensus will be arrived at. The final allocation of the data within the NASSS framework will be agreed by all authors. Rigour will be further enhanced via a reflexivity statement by the researchers involved in the coding and analysis. Qualitative data will be reported according to the consolidated criteria for reporting qualitative research checklist.^23^

### Health economic methodology and analysis

A comprehensive health economic analysis will assess the cost-effectiveness of the remote model across settings. This will include an examination of NHS costs for training, equipment and service delivery (current tariffs), alongside economic benefits derived from improved patient outcomes and system efficiencies. Productivity will be assessed from both NHS and patients’ perspectives. Health utility will be assessed via PROMs and successful treatment/discharge from ENT care. Cost-consequence and cost-utility analyses will be undertaken in line with NICE guidelines.^24^ Data will be standardised and allocated to clinical pathways, with incremental cost-effectiveness ratios generated to compare models. Results will be summarised descriptively for each cost category, highlighting any pathways with a significant impact on overall costs or outcomes.

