### Quantitative methodology

Quantitative methodology study process using questionnaires (figure 2):

Patients attending traditional pathway and new remote pathway recruited.Remote pathway participants: two questionnaires - first on the day of clinic attendance and second after completion of treatment or discharge.Traditional pathway participants: one questionnaire on the day of clinic attendance.

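### Successful treatment or discharge is listed, beside PROMs, as a measure of health utility for the cost-utility analysis, and the questionnaire schedule could leave it as the only later utility input in both groups

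*Protocol article*

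**What the plan says.** The section on health economic methodology gives the measure: "Health utility will be assessed via PROMs and successful treatment/discharge from ENT care". It then says "Cost-consequence and cost-utility analyses will be undertaken in line with NICE guidelines", and that data will be allocated to pathways "with incremental cost-effectiveness ratios generated to compare models". The list of secondary outcomes repeats the plan ("Perform cost-consequence and cost-utility analyses from an NHS perspective") and adds a second economic item: "Conduct a cost-consequences analysis detailing waiting times, quality of life, resource use, costs, time off work and productivity for both study groups".

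The questionnaire schedule is in the section on quantitative methodology. Remote participants complete two, the "first on the day of clinic attendance and second after completion of treatment or discharge". For the other group the text is "Traditional pathway participants: one questionnaire on the day of clinic attendance". The Recruitment section describes the second remote questionnaire as "asking for their overall experience of the new service". It also says that primary outcome data come from the clinical notes and secondary outcome data from questionnaires.

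**The concern.** A cost-utility analysis needs, on its effect side, a value attached to a health state by preference and followed over time in each group. Discharge from a specialist service records that the service has finished with the patient. It carries no preference weight and does not say how well the patient is. Naming it as a way to assess utility is therefore a wrong choice of measure, which is different from leaving an instrument unnamed. The point follows from what a cost-utility analysis is and does not depend on the detail of the NICE guidance.

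Cost-effectiveness is one of the study's stated aims. If discharge enters the effect side of the ratio, service efficiency is counted as health. Waiting times and discharge rates are already compared in their own right, so the same feature of the pathway would appear once as a process result and again as health gain.

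**Working it through.** The article gives no utility value, QALY or ratio, so there is no figure to reproduce. The check has two parts.

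**1. What the described schedule can supply**

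| Possible utility input | Remote group | Traditional group |
|---|---|---|
| Questionnaire on clinic day | yes | yes |
| Questionnaire after treatment or discharge | yes, described as asking about experience | none |
| Treatment or discharge status | obtainable | obtainable |

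The economic analysis is a secondary outcome, and secondary outcome data are to come from questionnaires. The last row assumes that status can be read from the notes in both groups. This is plausible, because the section on quantitative analysis lists discharge rates among the quantities examined.

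On this schedule no PROM is collected after the clinic day in the traditional group, so a change in PROM-based utility cannot be compared between groups. The one row that is filled for both groups after baseline is treatment or discharge status, which is the input that is not a utility.

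**2. Whether scoring discharge would favour a quicker pathway**

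All inputs here are assumptions: identical true health in both groups, discharged = 1, not discharged = 0, horizon H = 52 weeks, and discharge supplying a share w of the utility score.

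If discharge is weighted by time, the spurious gain is w × (t_slow − t_fast) / H.

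With w = 1:
- 4 against 8 weeks: 4 / 52 = 0.077
- 8 against 16 weeks: 8 / 52 = 0.154
- 12 against 24 weeks: 12 / 52 = 0.231

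For 12 against 24 weeks with other shares:
- w = 0: 0
- w = 0.25: 0.25 × 0.231 = 0.058
- w = 0.5: 0.5 × 0.231 = 0.115

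If discharge is scored only as status at the end of the pathway and everyone is eventually discharged, the difference is 1 − 1 = 0. If it is read at a fixed time between the two discharge times, one group scores 1 and the other 0, again with no difference in health.

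So the direction and size of any bias depend on how discharge is scored, on its share and on when it is read. The article states none of these.

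**The case against.** The strongest reply is that the sentence is condensed. PROMs are named first, quality of life is listed separately for both groups, and a cost-consequence analysis is planned beside the cost-utility analysis. One could read it as PROMs feeding the utility analysis and discharge feeding the cost-consequence analysis. The instrument, value set and QALY method may be in the full protocol or an economic plan, and their absence from an article is not a fault. Economic analysis is also a secondary outcome, and the cost-consequence part is unaffected.

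Much of this stands. A QALY from a preference-based PROM is not excluded, and nothing here counts against the article for leaving the instrument unnamed. The reply does not remove the point, because the sentence assigns discharge to health utility in so many words. The benign reading also relies on a PROM comparison after baseline that the described schedule does not provide.

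The single questionnaire in the traditional group is a problem in its own right and would remain if discharge were deleted from the sentence. It is used here because it decides whether PROMs could carry the analysis.

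A reader might go further and infer three things that the article does not support:
- **The ratios will not be cost per QALY.** The denominator is not stated, so this can only be said of a ratio that includes discharge.
- **The analysis favours faster discharge by construction.** No scoring rule is given, the article does not say which pathway discharges sooner, and under end-status scoring the effect can be zero.
- **Failed discharges in the remote group would be hidden.** Re-presentation of remote-clinic patients is assessed under the primary outcome, and symptom resolution is analysed separately from discharge rates.

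**Conclusion.** The point holds in a limited form. Treatment success or discharge is wrongly named as a measure of health utility, and a ratio that includes it in the effect is not a cost per QALY. It could credit a quicker pathway without health gain if discharge is time-weighted or read before both pathways finish. The described schedule makes this more than a slip of wording, since it could leave discharge status as the only utility input after baseline that both groups share.

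No size of bias can be derived from the article. The range of 0 to 0.231 utility-years rests wholly on the assumed discharge times, horizon and shares with time-weighted scoring, and shows only that the result turns on an unstated rule. A ratio in pounds cannot be illustrated without inventing a cost difference, and the article does not give even its sign. What is at risk is the cost-utility result. The cost-consequence analysis is sound on this point.

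**What to change.** - Remove successful treatment and discharge from the sentence on health utility, and report them as separate consequences in the planned cost-consequence analysis.
- State that utility and QALYs come only from a preference-based PROM (EQ-5D-5L is one example), collected at matching times in both groups: at attendance and at one later time point fixed from attendance, so that discharge itself does not set the timing.
- If the traditional group is not followed up, report cost-consequences only and drop the cost-utility analysis and its ratios.

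The first change costs only wording in the protocol and economic plan. The second costs one short follow-up form for the traditional group, and possibly a short instrument in the existing questionnaires, whose content the article does not list. As ethical approval has been granted, the extra form would presumably need an amendment. The third costs the cost-utility result.
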